#### ^166^Ho-PLLA-MS safety dose

The second angiography takes place around 1 week after the first angiography but no longer than 2 weeks later. Patients will be hospitalized on the evening before the day of treatment. They will be discharged approximately 48 hours after the intervention unless complications have occurred. Prior to the procedure, the patient is offered a tranquilizer (oxazepam 10 mg)**. **A safety dose of ^166^Ho-PLLA-MS will be administered through a catheter inside the hepatic artery, at the position planned during the first intervention. The safety dose will consist of 60 mg (10% of the total amount of microspheres) ^166^HoPLLA-MS with a lower specific activity (90 Bq/microsphere) than for the treatment dose. After the safety dose, planar imaging of both the thorax and abdomen will be performed, as well as SPECT and MRI of the abdomen. Presence of inadvertent administration to the lungs or other upper abdominal organs will once more be checked for. These SPECT and MRI images will be compared with the images post ^99m^Tc-MAA and post-treatment, regarding extrahepatic deposition of activity, percentage lung shunting, homogeneity of the dose distribution and tumour to healthy tissue absorbed dose ratio.

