#### Macroaggregated albumin injection

After successful angiography and coiling of relevant vasculature is performed, a dose of ^99m^Tc-Macroaggregated Albumin ( ^99m^Tc-MAA) will be administered in the hepatic artery on the same day. The ^99m^Tc-MAA are used to assess whether a favourable distribution of the ^166^Ho-PLLA-MS can be expected. The patient is subjected to planar imaging of the thorax and abdomen and SPECT of the abdomen, in order to determine the ^99m^Tc-MAA distribution. Images will be evaluated qualitatively and quantitatively. Extrahepatic deposition of activity is a contra-indication for administration of the treatment dose. Region of interest analysis will be used to calculate lung shunting. Lung shunting should not exceed 20% of the dose ^99m^Tc-MAA. If the amount of lung shunting cannot be reduced to <20% using standard radiological interventional techniques to decrease the shunting, the patient will not be eligible to receive a safety nor a treatment dose of ^166^Ho-PLLA-MS. The dose point-kernel method will be applied to the (non-homogeneous) activity distribution to calculate the absorbed dose distribution [25]. Dose-volume histograms will be generated in order to quantify the dose distribution, and the tumour to healthy tissue absorbed dose ratio will be calculated.

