### Secondary objectives

Secondary objectives are to evaluate tumour response, performance status, biodistribution, quality of life and to compare the accuracy of the ^99m^Tc-MAA scout dose with a safety dose of ^166^Ho-PLLA-MS, in predicting microsphere distribution of the treatment dose. Tumour response will be quantified using CT of the liver scored according to Response Evaluation Criteria in Solid Tumours guidelines (RECIST 1.1) [27]. Tumour viability will be assessed by PET, depending on tumour type. In addition, the antitumoral effect will be assessed by relevant tumour markers responses if applicable (i.e. carcinoembryonic antigen (CEA) in colorectal carcinoma and chromogranin A (CgA) for neuroendocrine tumours). Biodistribution is assessed using quantitative SPECT and MRI. Urine and blood samples will be screened for presence of ^166^Ho-PLLA-MS or fragments of ^166^Ho-PLLA-MS. Performance status is assessed using WHO performance status criteria. Quality of life (QoL) is evaluated using the EORTC questionnaire QLQ-C30 with colorectal liver metastases module QLQ-LMC21. Finally, the accuracy of the ^166^Ho-PLLA-MS safety dose in predicting the distribution of the treatment dose is compared with the accuracy of the ^99m^Tc-MAA. Quantitative SPECT analysis will be performed using the scatter correction method described by De Wit *et al*. [14].

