### Statistical considerations

Descriptive statistics (n, mean, standard deviation, median, minimum and maximum) will be calculated for each quantitative variable; frequency counts by category will be made for each qualitative variable. Interim analysis will be performed after every 3 patients. Inclusion of patients in the next cohort will be performed if the Independent Data Monitoring Committee (IDMC) has scrutinized the toxicity data and given permission to proceed.

Two sets of study data will be evaluated: the primary objective will be evaluated in the full analysis set (FAS). The FAS is defined as the set of data generated from the included patients who received at least the safety dose. The secondary objectives will be evaluated in both FAS and per-protocol set (PPS). The PPS is defined as the set of data generated from the included patients who complied with the protocol.

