Hepatic arterial injection with ^99m^Tc-MAA and subsequent scintigraphic imaging is widely used to predict the biodistribution of ^90^Y microspheres, prior to the actual radioembolization procedure. Its accuracy can however be disputed. In our centre, we have observed that patients with a borderline lung shunt fraction of 10% to 19%, as calculated using the ^99m^Tc-MAA images (approximately 24% of all patients, all of whom were instilled a by 50% reduced amount of radioactivity), had no signs of lung shunting on post- ^90^Y-RE Bremsstrahlung images. In these cases, it seems that the ^99m^Tc-MAA-scan had false-positively predicted extrahepatic spread. This may be explained by the fact that ^99m^Tc-MAA differs in many aspects from the microspheres that are used. Shape, size, density, in-vivo half-life, and number of ^99m^Tc-MAA particles do not resemble the microspheres in any way [13,31]. In addition, free technetium that is released from the MAA particles can disturb the (correct) assessment of extrahepatic spread. We hypothesize that a small safety dose with low-activity ^166^Ho-PLLA-MS will be a more accurate predictor of distribution than ^99m^Tc-MAA. The unique characteristics of ^166^Ho-microspheres, in theory, allow a more accurate prediction of the distribution with the use of scintigraphy and MRI. In this study, we chose to perform both an injection with ^99m^Tc-MAA and administration of a safety dose of ^166^Ho-PLLA-MS. The respective distributions of the ^99m^Tc-MAA and the ^166^Ho-PLLA-MS safety dose will be compared with the distribution of the treatment dose of ^166^Ho-PLLA-MS by quantitative analysis of the scintigraphic images.

Both commercially available ^90^Y-MS products are approved by the Food and Drug Administration (FDA) and European Medicines Agency as a medical device and not as a drug. Radioactive microspheres are a medical device since these implants do not achieve any of their primary intended purposes through chemical action within or on the body and are not dependent upon being metabolized for the achievement of their primary intended purpose. In accordance with the definition of a medical device by the FDA and in analogy with the ^90^Y-MS, we consider the ^166^Ho-PLLA-MS to be a medical device [32]. The Dutch medicine evaluation board has discussed this issue (13 July 2007) and has concluded that the microspheres are indeed to be considered as a medical device.

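### The listed intrahepatic measures do not test spatial agreement within the liver, although the MAA versus holmium-scout objective is accuracy in predicting the distribution

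*Protocol article*

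**What the plan says.** All references are to the protocol article.

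- **Objective.** *Secondary objectives* compares the accuracy of the MAA scout with that of the holmium safety dose "in predicting microsphere distribution of the treatment dose". The *Discussion* states the hypothesis that a small low-activity holmium dose "will be a more accurate predictor of distribution than" MAA, and says that each scout's distribution will be set against that of the treatment dose "by quantitative analysis of the scintigraphic images".
- **Measures.** The section on the safety dose compares its SPECT and MRI images with those after MAA and after treatment on four items: "extrahepatic deposition of activity, percentage lung shunting, homogeneity of the dose distribution and tumour to healthy tissue absorbed dose ratio".
- **Summary of the MAA images.** *Macroaggregated albumin injection* says: "Dose-volume histograms will be generated in order to quantify the dose distribution, and the tumour to healthy tissue absorbed dose ratio will be calculated". It also says: "Images will be evaluated qualitatively and quantitatively".
- **Technical detail.** *Secondary objectives* adds only this: "Quantitative SPECT analysis will be performed using the scatter correction method described by" a cited paper, which the *Background* cites for holmium dosimetry.
- **Statistics.** *Statistical considerations* is generic: "Descriptive statistics (n, mean, standard deviation, median, minimum and maximum) will be calculated for each quantitative variable". No error rate, power or rule for judging one scout the better predictor is given for this comparison.

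**The concern.** The objective is about location: does the scout go where the treatment dose later goes? Inside the liver, the two named measures describe how uneven the dose is and how much tumour receives relative to healthy tissue. Neither asks whether the same lesions or the same lobe are hot on both images. The dose-volume histogram has the same limit, because it discards position.

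This matters for these patients. The *Background* notes that hepatic metastases are often multiple, and Appendix 1 requires that the whole liver can be treated by one administration, so distribution between lesions and lobes is much of what a scout has to predict.

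The two organ-level measures only partly fill the gap. Extrahepatic MAA activity rules out the treatment dose, and a lung shunt that cannot be brought below 20% bars both holmium doses. Among patients who have a post-treatment image, these two measures therefore have a restricted range, and much of the comparison falls on the intrahepatic measures. At stake is the first of the advantages over yttrium set out in the *Background*: better prediction by a holmium scout.

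**Working it through.** The document gives no figure for this comparison, so there is nothing of the plan's own to reproduce. The check is whether the named measures respond to location. All values in steps 1 and 2 are illustrative assumptions.

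**1. Two equal lesions.** Lesion-to-normal ratios are 6 and 2 on the scout, and 2 and 6 after treatment.

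- Pooled ratio: scout (6 + 2)/2 = 4.0; treatment (2 + 6)/2 = 4.0.
- Homogeneity is the same, because the set of values is the same.
- Lesion errors: 6/2 - 1 = +200%; 2/6 - 1 = -67%.

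**2. An illustrative liver.** Eight segments of 100 voxels; four equal lesions of 10 voxels in alternate segments, with three times the normal uptake; random voxel variation; one half of the liver hot and the other cold (factors 1.6 and 0.4); mean dose 60 Gy. Scout A has the treatment pattern with 10% noise. Scout B has the same voxel values with the two halves exchanged. Scout C has no tumour preference. Homogeneity is taken as the coefficient of variation (CV), and the ratio is pooled over lesions.

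| Image | CV | Tumour/healthy ratio | Minimum dose to 70% of volume (Gy) | Volume above 40 Gy | Voxel correlation with treatment |
|---|---|---|---|---|---|
| Treatment | 0.874 | 3.275 | 23.1 | 52.9% | 1 |
| A, right place | 0.880 | 3.243 | 23.5 | 52.5% | 0.987 |
| B, wrong half | 0.874 | 3.275 | 23.1 | 52.9% | -0.306 |
| C, no tumour preference | 0.705 | 0.923 | 24.4 | 51.1% | not computed |

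B equals treatment on every location-free summary, and A differs slightly, so these summaries rank the wrong scout first. B's lesion means are 67.7, 71.3, 277.7 and 289.0 Gy, against 277.7, 289.0, 67.7 and 71.3 Gy at treatment. For the first lesion the error is 67.7/277.7 - 1 = -76%; for the third it is 277.7/67.7 - 1 = +310%. C shows what the ratio does detect: 0.923 against 3.275.

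**3. Would a regional measure separate A from B?** The segments are of equal size, so a segment's share is its mean dose divided by the sum of the eight means, which is 480.0 Gy.

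- Treatment segment means: 104.5, 87.1, 103.7, 87.5, 27.6, 21.9, 26.6, 21.1.
- Scout A: 105.2, 86.8, 102.5, 87.9, 27.7, 22.0, 26.5, 21.4. Absolute differences sum to 0.7 + 0.3 + 1.2 + 0.4 + 0.1 + 0.1 + 0.1 + 0.3 = 3.2. Mean error in share: 3.2/(8 × 480.0) = 0.08 percentage points.
- Scout B: the differences are 76.9, 65.2, 77.1 and 66.4, each occurring twice, and sum to 2 × 285.6 = 571.2. Mean error in share: 571.2/(8 × 480.0) = 14.9 percentage points.

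The average share is 100/8 = 12.5%, so B's error is larger than an average segment's whole share. The regional measure separates the two scouts clearly.

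**The case against.** **The measures are not blind to misplacement in general.** This is right. Extrahepatic deposition and lung shunt concern the wrong organ, and the ratio separates tumour from healthy tissue. A reader might infer that the comparison cannot show which scout predicts better, or is uninterpretable. The document does not support that. The *Discussion* motivates the hypothesis partly with apparently false-positive MAA lung shunts of 10% to 19%. Those patients lie below the 20% limit and can reach treatment, so the lung-shunt measure tests that claim directly.

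**An article is not an analysis plan.** The text does not exclude lesion-level or voxel-level work, MAA images are also read qualitatively, and nothing says that the ratio is pooled. If it is computed per lesion and matched between images, the lesion-swap example fails for the ratio. This stands as a condition on the finding. What remains is that the article names its measures, and none of them is a measure of spatial agreement within the liver.

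**An exact swap is a limiting case.** The catheter goes to the position planned at the first angiography, and one hepatic-artery administration covers the liver. The examples show what the measures cannot see, not how often it would happen.

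**Two further inferences should not be drawn.** First, the generic descriptive statistics do not rule out a paired analysis: nothing forbids summarising within-patient differences, and the images are compared within patient already. Second, a reader might infer that MAA must look worse because the holmium scout and the reference share a radionuclide. Such a bias is plausible, but the document gives no resolution or recovery figures from which to size it. Nor do the two holmium images necessarily have equal quality: 600 mg at up to 450 Bq per sphere against 60 mg at 90 Bq is (600/60) × (450/90) = up to 50 times the activity.

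**Conclusion.** The point holds in a limited form. Homogeneity does not test spatial agreement within the liver, and neither does the tumour-to-healthy ratio if it is pooled over lesions. A scout that sends activity to the wrong lesions or lobe can match the treatment image on both, while the stated objective is accuracy in predicting the distribution. The list still detects wrong-organ and tumour-versus-healthy misplacement.

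The illustration shows that the gap can be complete (an exact match with a voxel correlation of -0.306), but its inputs are assumed and it says nothing about frequency. The size of any imaging-related bias against MAA cannot be derived from the document. This is a minor point on a secondary, descriptive objective in a study of 15 to 24 patients. The maximum tolerated dose and the escalation decisions are unaffected.

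**What to change.** Keep the four listed measures as descriptive and add one spatial agreement measure per patient:

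1. Register the MAA, safety-dose and treatment SPECT to the baseline CT, and apply one set of non-overlapping lesion and segment regions to all three.
2. For each scout, compute the mean over regions of |scout share - treatment share| of liver activity.
3. Per patient, take the MAA error minus the holmium error. Report the typical difference with a 95% interval (Hodges-Lehmann, or a bootstrap by patient) in patients with all three images.
4. As a sensitivity check, repeat this with the MAA and holmium images brought to a common resolution, each with scatter correction suited to its radionuclide.

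Also state whether the tumour-to-healthy ratio is pooled or computed per lesion.

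The cost is extra image analysis on images already planned, with no added patient burden. Registration error adds some noise, mainly for small lesions, and the interval will be wide at this sample size.

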### Treatment

#### ^166^Ho-PLLA-MS treatment dose

When the amount of lung shunting does not exceed 20% of the safety dose of ^166^HoPLLA-MS, the (complete) treatment dose of ^166^HoPLLA-MS will be administered (Figure 2). Consecutive cohorts of 3 patients will be treated with identical amounts of microspheres (600 mg), and the last cohort will consist of at least 6 patients. If no toxicity ≥ grade 3 according to the Common Terminology Criteria for Adverse Events (CTCAE)[26] is observed, the next cohort of three patients will be treated at the next radiation dose level. If in one patient CTCAE ≥ grade 3 is observed in a particular cohort, the cohort will be extended to six patients. If toxicity ≥ grade 3 is observed in two or more patients in a particular cohort, the study will be terminated because the endpoint, e.g. the maximum tolerated radiation dose, is reached. This will be reported to the Independent Ethics Committee (IEC). The dose level prior to the toxic radiation dose will become the recommended dose for efficacy studies. If an event is classified as grade 3 or 4 administration technique related, the patient will be replaced. The specific activity of the ^166^Ho-PLLA-MS will be increased by adapting the activation time in the nuclear reactor. The first, second, third and fourth cohort will be treated with a dose of 1.3, 2.5, 3.8 and 5.0 GBq/kg (liver weight), respectively. Assuming a homogenous uptake throughout the liver, this equals escalating radiation doses of 20 Gy, 40 Gy and 60 Gy, to a maximum dose of 80 Gy in the last cohort. A maximum of 15.1 GBq will be given to the maximum treated liver weight (inclusive the tumour tissue) of 3 kg (Table 2). The amount of radioactivity administered to the patient is calculated according to the following formula:

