## Methods

### Study design

The HEPAR study is a single centre, non-randomized, open label safety study. In this phase I study, a new device will be investigated, namely ^166^Ho-PLLA-MS for intra-arterial radioembolisation for the treatment of liver malignancies. In a group of 15 to 24 patients with liver metastases, treated with increasing amounts of ^166^Ho, the device will be investigated for safety and toxicity.

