One important issue concerning the resin-based SIR-Spheres ^® ^is the relatively high number of particles instilled (>1,000 mg), since this may sometimes be associated with macroscopic embolization as observed during the fluoroscopic guidance [28,33]. Several authors have reported stasis of flow during administration of resin microspheres and were forced to end the procedure prematurely because of the risk of backflow, hence extrahepatic deposition of a part of the dosage [28,34,35]. The specific activity of the ^166^Ho-PLLA-MS is considerably higher than that of the resin microspheres (≤450 and 50 Bq/microspheres, respectively). However, in order to obtain an equivalent absorbed dose, the total amount of radioactivity of the administered microspheres in ^166^Ho radioembolization needs to be 3 times higher than in ^90^Y radioembolization, due to the shorter physical half-life of ^166^Ho. Even so, compared with the resin ^90^Y microspheres, in ^166^Ho radioembolization considerably less microspheres (≤600 mg) are used to obtain an equivalent radiation dose, resulting in a lower risk of stasis or backflow during administration [9,29]. A further issue is that ^90^Y microspheres can not be visualized under fluoroscopy during injection. Manufacturers of resin ^90^Y microspheres state that their microspheres are to be administered with water for injection alternated with non-ionogenic contrast [36]. As a result, the operating physician cannot detect stasis or backflow of microspheres until he has switched from injecting microspheres to injecting the contrast agent. Holmium microspheres, on the contrary, are administered in a mixture of 50% saline and 50% non-ionogenic contrast under constant fluoroscopic imaging, which ensures constant control over the microspheres during injection [37]. However, continuous fluoroscopic imaging during microsphere administration may comprise an increased radiation dose delivered to the patient, specifically the abdominal skin, during the procedure. 	

If this phase I trial provides sufficient data to prove that ^166^Ho-PLLA-RE has an acceptable safety and toxicity profile, further studies will be needed. The next step will be an efficacy study in a larger number of patients. The primary endpoints of that study will be tumour response and survival.

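### The evidence for escalation and the MTD is not tied to delivered activity, so a patient with an incomplete infusion and no toxicity stays in and is not replaced

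*Protocol article*

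**What the plan says.** In the protocol article, the subsection on the 166Ho-PLLA-MS treatment dose sets the cohort rules:

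- **Planned treatment.** "Consecutive cohorts of 3 patients will be treated with identical amounts of microspheres (600 mg". For the highest level the article makes an exception: "the last cohort will consist of at least 6 patients". The levels are 1.3, 2.5, 3.8 and 5.0 GBq per kg of liver, equated with 20, 40, 60 and 80 Gy. Table 2 gives the matching activities.
- **Escalation.** When no grade 3 or worse toxicity "is observed, the next cohort of three patients will be treated at the next radiation dose level". With one such patient "the cohort will be extended to six patients". With two or more the study stops and the maximum tolerated radiation dose (MTD) is taken as reached.
- **Replacement.** "If an event is classified as grade 3 or 4 administration technique related, the patient will be replaced". No other ground for replacement is given.

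Under Statistical considerations, the primary objective is evaluated in the full analysis set (FAS), which takes in every included patient given at least the safety dose. The per-protocol set is used only for secondary objectives. The Independent Data Monitoring Committee (IDMC) must review the toxicity data and agree before the next cohort opens.

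The Discussion reports that operators using resin microspheres "were forced to end the procedure prematurely because of the risk of backflow, hence extrahepatic deposition of a part of the dosage". It expects the smaller quantity of holmium microspheres to do better, "resulting in a lower risk of stasis or backflow during administration", and describes continuous fluoroscopic control during injection.

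**The concern.** The primary result is a radiation dose in Gy, and the level below the toxic one becomes the recommended dose for efficacy studies. A patient who received only part of the planned activity is evidence about a lower dose. If that patient has no toxicity, none of the stated rules removes the patient or adjusts for what was delivered:

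- escalation looks only at toxicity counts;
- replacement looks only at technique-related grade 3 or 4 events;
- the FAS looks only at receipt of the safety dose.

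The per-protocol set could screen out incomplete treatment but is not used for the primary objective. The rules are therefore uneven. A technique problem that produces a severe event leads to replacement, whereas one that produces underdosing without an event does not.

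With three to six patients per level, a single non-event carries weight. At 20, 40 or 60 Gy it can support moving up. At 80 Gy, where there is no higher level, it can support declaring the level tolerated.

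**Working it through.** **The plan's own figures.** Four cohorts with "In a group of 15 to 24 patients with liver metastases": the minimum is 3 + 3 + 3 + 6 = 15 and the maximum is 4 × 6 = 24. Both reproduce. Table 2 follows from A = D × LW / 0.01587, with A in MBq, D in Gy and LW in kg. For 20 Gy and 1.5 kg this is 20 × 1.5 / 0.01587 = 1890 MBq, as stated. The bold rows agree within 3 MBq.

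**What a half infusion delivers** (Table 2, 1-kg liver, uniform uptake as the article assumes):

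- 80 Gy level: 5040 / 2 = 2520 MBq, the 40 Gy row.
- 60 Gy level: 3780 / 2 = 1890 MBq, the 30 Gy row.
- 40 Gy level: 2520 / 2 = 1260 MBq, the 20 Gy row.

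One such patient of three at 60 Gy makes the cohort mean (60 + 60 + 30) / 3 = 50 Gy. One of six at 80 Gy makes it (5 × 80 + 40) / 6 = 73.3 Gy.

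**Chance of escalating from 20, 40 or 60 Gy.** The article gives no toxicity rate and no rate of incomplete infusion, so the rates below are assumptions. The rule, reading one event in six as permission to proceed, is

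P(escalate) = P(0 of 3) + P(exactly 1 of 3) × P(0 of next 3).

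Let p be the toxicity rate at full dose and p_u the rate in one underdosed patient among the first three. For p = 0.40:

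- All at full dose: 0.6³ + (3 × 0.4 × 0.6²) × 0.6³ = 0.216 + 0.432 × 0.216 = 0.309.
- One underdosed, p_u = 0.10: P(0 of 3) = 0.9 × 0.36 = 0.324; P(1 of 3) = 0.1 × 0.36 + 0.9 × 0.48 = 0.468; total 0.324 + 0.468 × 0.216 = 0.425.
- One underdosed, p_u = 0: 0.36 + 0.48 × 0.216 = 0.464.

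| p (assumed) | All at full dose | One underdosed, p_u = 0.10 | One underdosed, p_u = 0 |
|---|---|---|---|
| 0.30 | 0.494 | 0.587 | 0.634 |
| 0.40 | 0.309 | 0.425 | 0.464 |
| 0.50 | 0.172 | 0.284 | 0.312 |

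One such patient adds about 9 to 16 percentage points.

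**Allowing for frequency.** The table is conditional on the event having happened. If instead each patient has an assumed chance u of an incomplete infusion, the chance of escalating at p = 0.40 (0.309 with none) is:

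| u (assumed) | p_u = 0.10 | p_u = 0 |
|---|---|---|
| 5% | 0.334 | 0.343 |
| 10% | 0.360 | 0.378 |
| 20% | 0.415 | 0.454 |

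**Chance of declaring 80 Gy tolerated** (at most one event in six; assumed rates 33% at full dose and 10% in one underdosed patient):

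- All at full dose: 0.67⁶ + 6 × 0.33 × 0.67⁵ = 0.090 + 0.267 = 0.36.
- One underdosed: 0.9 × 0.67⁵ + 0.1 × 0.67⁵ + 0.9 × 5 × 0.33 × 0.67⁴ = 0.122 + 0.014 + 0.299 = 0.43.

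**How little the FAS requires.** The safety dose is 60 mg, 10% of the total, at 90 Bq per microsphere. Taking 10% of the 33 million particles in Table 1, that is 3.3 million × 90 Bq = 297 MBq, or 297 × 0.01587 / 1.5 = 3.1 Gy in a 1.5-kg liver. FAS membership therefore says almost nothing about exposure at the cohort's level.

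**The case against.** The strongest reply is that the article never says how an incomplete infusion is handled. A reader might infer that it counts such a patient as treated at the full planned dose, but no sentence says so. The treatment subsection presupposes that the whole dose is given, and an article may leave evaluability to the full protocol. This stands against any claim that the sponsor has adopted such a rule. It does not dispose of the point, because the article does state the escalation, replacement and analysis-set rules. Followed literally, they keep this patient in and give no ground for replacement.

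The event is also borrowed. Early termination is reported for resin microspheres at more than 1,000 mg, against at most 600 mg here, and a lower risk is expected. A reader might infer that the same problem will be common with holmium, and the article does not support that. A lower risk is not no risk, however, and fluoroscopy helps the operator see stasis rather than guaranteeing full delivery.

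Safeguards exist. The IDMC must agree before each next cohort and may recommend process changes, and quantitative SPECT and MRI are planned. The IDMC could therefore take delivered dose into account, but what it is described as receiving is toxicity data.

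Two further readings go too far. The three-patient arithmetic and the escalation probabilities do not carry over to 80 Gy, because that cohort has at least six patients and no level above it. Nor does replacing patients with technique-related events make the MTD too high by itself, since it keeps events not driven by dose out of a dose-finding result and the substitute can still show toxicity.

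**Conclusion.** The point holds as a gap between stated rules that should be closed before cohort 1. The escalation and MTD evidence is not tied to delivered activity, and an underdosed patient without toxicity biases the result towards escalation or towards a finding of tolerance.

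Under assumed toxicity rates of 30% to 50%, one such patient among the first three adds 9 to 16 points to the chance of escalating. At 80 Gy the illustrative change is from 0.36 to 0.43. These sizes depend on assumed toxicity rates and on the event occurring. With a 5% chance per patient, the effect at 40% toxicity is only about 3 points.

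A reader might conclude that the MTD will be falsely high. The documents do not support that. They give no rate of incomplete infusion, they expect a low risk, and the IDMC may intervene. An inflated MTD is possible, not established.

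**What to change.** In the treatment-dose subsection, define a set evaluable for escalation and the MTD, separate from the FAS. It should contain patients who received at least a stated share of their planned activity, together with any patient who had a dose-limiting toxicity whatever share was received. The sponsor sets the share before cohort 1; none is proposed here.

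- Replace toxicity-free patients below the share through the existing replacement mechanism, so that they do not count towards the three or six.
- Measure residual activity after each infusion, cross-check delivery with the SPECT already planned, and give the IDMC each patient's delivered activity and absorbed dose. Report the same figures beside the MTD. The MTD stays a cohort level, because individual delivered doses describe the evidence and do not select the level in this design.
- Reconcile the treatment-dose subsection with Statistical considerations. The FAS can remain the set for describing safety.

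The cost is protocol wording, one residual measurement per infusion and an occasional replacement patient. Replacements would come on top of the 15 to 24, which covers only cohorts of three to six.
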